### Data analysis

Multilevel analysis will be used to estimate the overall effect of podiatric treatment as compared to standardised shoe advice on the three primary outcome measures (PI-NTR, FFI-5pt and FPDI). Both clustering due to participants being treated by podiatrists and clustering due to repeated measurements within the same individuals will be taken into account. Results will be adjusted for differences in baseline similarity, if these occur. The effect of interest is the treatment × time interaction [32] where the primary focus will be on the primary outcome measures at 3 and 12 months' follow-up. Differences in secondary outcome will be estimated using similar statistical methods. All data will be analysed using an intention-to-treat approach. In all cases, a significance level of 5% is pre-stipulated.

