### Control condition

Participants (n = 100; see Sample size) in the control group will receive a leaflet with shoe advice. The leaflet has been developed in cooperation with the GPs of the Academic Network of the VU University medical centre, the podiatric school of Fontys University of Applied Sciences and 8 podiatrists in the region. Shoe advice is part of the lifestyle advice that is frequently given by GPs to patients with foot problems [13]. Discussions with GPs prior to the trial indicated that this reflects a common minimal and first treatment option; general advice is given to wear well-fitting shoes of good quality and sometimes the patient's shoes are checked and commented on. Some GPs give more specific advice to adapt the shoe or to buy custom made shoe inlays or orthoses. In order to reflect usual care while ensuring optimal contrast between the two treatment groups, we will ask the GPs to refrain from specific individual advice. The participants will be advised to compare their shoes with recommended shoe wear presented in the leaflet and to purchase better fitting shoes if their shoes are not compatible with these recommendations. A reimbursement of € 25,- is given as an encouragement. All patients are invited to contact the research group or their GP for questions regarding the information leaflet. All participating GPs will receive a brief training session on how to provide information based on the leaflet and how to perform a shoe assessment.

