### Sample size

There are no evidence-based estimates for clinically important change in assessing forefoot pain or for clinically relevant differences between interventions for chronic foot pain. In a previous study it was estimated that a reduction of approximately two points on an 11-point pain intensity numerical rating scale represents a clinically important improvement [29]. We assume that the improvement in the podiatric treatment group will be one point larger than the improvement in the control group (a mean improvement of approximately 2 versus 1 point on the 0-11 point NRS, with an estimated standard deviation of 2.5). In this design the main question is "whether the podiatric treatment is more effective than the control treatment viz. a standardised shoe advice". Therefore we will perform a one-sided statistical test with the null hypothesis that podiatric treatment has either an equal outcome or a worse outcome as compared to standardised shoe advice, both outcomes having an equal clinical consequence [30].

In order to detect a 1 point difference in improvement between the groups after 12 months with a one-sided significance level of 0.05, and assuming a power of 0.8, an ICC between podiatrists and GPs of 0.05, a correlation of 0.50 between repeated measurements and a minimum of 5 patients per care provider, we would need complete data of 75 participants in each study group. We will enrol 2 × 100 patients to allow for a drop-out rate during follow-up of 25%. If every podiatrist will treat a minimum of 5 patients, 15 podiatrists will be needed to deliver the treatment in the entire intervention group.

In 17 practices of the Academic Network, with a total of n = 23,231 patients of 50 years or older, the diagnosis "foot problems" (ICPC 17) or free text words indicating foot problems were noted in the GP records of n = 497 patients within this age group. This incidence (21/1000) is in accordance with a previous estimate of 17/1000 [31]). We expect that about one third of all consulters presenting with foot problems have forefoot problems that meet our criteria [2,5], and assuming about 50% of these patients are eligible and willing to participate, a practice with a population of average age distribution can generate a minimum of 5 participants per year. This means that we will need to recruit at least 40 practices to participate in the trial to achieve the required number of patients.

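### The sample size assumes provider clustering for GPs as well as podiatrists, but the analysis accounts for podiatrists and repeated measures only, so the clustering assumed for the control arm is left out

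*Protocol article*

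**What the plan says.** The Sample size section lists among its assumptions "assuming a power of 0.8, an ICC between podiatrists and GPs of 0.05, a correlation of 0.50 between repeated measurements", and continues with "a minimum of 5 patients per care provider, we would need complete data of 75 participants in each study group". One ICC and one cluster size thus serve both arms, with podiatrists and GPs both counted as providers.

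The Data analysis section states: "Both clustering due to participants being treated by podiatrists and clustering due to repeated measurements within the same individuals will be taken into account". It names no GP or practice level. The Discussion describes the therapist effect to be estimated as variation between podiatrists.

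Under Control condition, controls receive a standardised leaflet and are not referred to a podiatrist. The GP has a part in that arm: "All participating GPs will receive a brief training session on how to provide information based on the leaflet". GPs are also trained to assess shoes and are one contact for questions about the leaflet.

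**The concern.** The design pays for provider clustering in both arms, and the analysis accounts for it in one. The wording joins two named sources with both and and, so it reads as a complete list and not as a detail left open. If controls of the same GP do resemble one another in response, as the sample size supposes, a model without that level treats them as independent. The standard error of the treatment effect is then too small, and the test rejects slightly more often than its nominal level.

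All control participants lack the one provider level that the analysis names. The article does not say how they stand in relation to it, so the reader cannot tell which provider structure, if any, the control arm is meant to have.

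**Working it through.** **Inputs from the Sample size section.** The target is a "1 point difference in improvement between the groups after 12 months with a one-sided significance level of 0.05", with "a mean improvement of approximately 2 versus 1 point on the 0-11 point NRS, with an estimated standard deviation of 2.5". Power is 0.8, the ICC 0.05, the correlation 0.50, and there are at least 5 patients per provider. The plan needs 75 complete per arm, 100 enrolled per arm, at least 40 practices and 15 podiatrists. Randomisation is of individuals, stratified by gender and age (Treatment allocation and adherence).

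**The plan's own figure.**
- Unadjusted, one-sided: n = 2 × (1.645 + 0.842)² × 2.5² / 1² = 77.3 per arm.
- Design effect: 1 + (5 − 1) × 0.05 = 1.20.
- Baseline-adjustment factor: 1 − 0.50² = 0.75.
- Product: 77.3 × 0.75 × 1.20 = 69.6, so 70 per arm, or 14 clusters of 5. One further cluster gives 15 × 5 = 75.

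The article does not give its formula. No direct one-sided calculation with the design effect of 1.20 returns 75, but a cluster-rounded one does, so 75 is not called wrong here. The dropout step reproduces: 75 / 0.75 = 100.

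**Effect of omitting control-arm clustering.** With equal arms, the variance of the difference is proportional to the sum of the two design effects. Let D1 be that of the podiatry arm and D0 that of the control arm. The analysis as described uses D1 + 1.

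- Modelled SE / true SE = √[(D1 + 1) / (D1 + D0)].
- Actual one-sided error = 1 − Φ(1.645 × that ratio).
- D1 = 1.20 throughout, at ICC 0.05.

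*Control cluster size under planned recruitment.* 200 participants / 40 practices = 5 per practice over both arms. With unequal clusters, the design effect depends on the size-weighted mean. For a control with complete data, each of the other four patients in the practice is also a control with complete data with probability about 75/200 = 0.375. The expected cluster size is therefore 1 + 4 × 0.375 = 2.5.

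| Complete controls per GP or practice | D0 | Modelled / true SE | True SE larger by | One-sided error |
|---|---|---|---|---|
| 1.875 (plain mean, 75/40) | 1.044 | 0.990 | 1.0% | 5.2% |
| 2.5 (size-weighted, 40 practices) | 1.075 | √(2.2/2.275) = 0.983 | 1.7% | 5.3% |
| 5 (as in the sample size) | 1.20 | √(2.2/2.4) = 0.957 | 4.4% | 5.8% |

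*Range.* The ICC is an assumption of the plan. Taking 0.01 to 0.10 in both arms and 2.5 to 5 controls per GP, the SE ratio runs from 0.996 to 0.926 and the one-sided error from 5.1% to 6.4%.

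*Power at 75 per arm with the 0.75 factor.* It is 0.854 with podiatrist clustering only, 0.843 with D0 = 1.075 and 0.826 with D0 = 1.20.

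**GP effects shared by both arms.** A simulation of 40 practices of 5, ICC 0.05, with 100 individuals randomised to each arm irrespective of practice, gave a standard deviation of the difference of 0.1415. The naive value is √(2/100) = 0.1414. A practice effect common to both treatments therefore leaves the standard error essentially unchanged when it is ignored. The table applies only to GP variation specific to the control treatment.

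**The case against.** The strongest reply is that little clustering is to be expected in the control arm. The leaflet is standardised, GPs are asked not to give individual advice, and questions may go to the research group instead. An ICC of 0.05 in both arms may be plain caution in sizing that does not bind the analysis. This stands as a reason why the true effect may be close to nil. It does not remove the mismatch: the plan counts GPs as providers in one section and omits them without explanation in another.

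Four stronger readings are tempting, and the documents do not support them.

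- **The podiatrist level is invalid because controls lack one.** A level present in one arm only is not an error. The article's wording refers to participants treated by podiatrists, which fits a random effect confined to the podiatry arm.
- **Controls might be coded as a single cluster,** adding √(0.05 × 6.25) = 0.56 to the standard error of a 1-point effect. The article states no such coding, and it would make the standard error too large, not too small.
- **Recruitment through some 40 practices by itself makes the standard error too small.** Randomisation is of individuals, so the shared practice effect cancels, as the simulation shows.
- **Tests with about 15 podiatrists need small-sample degrees of freedom.** That is detail commonly left to a statistical analysis plan, which is not shown.

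**Conclusion.** The inconsistency is real and rests on explicit text in two sections. Its numerical consequence is small: about 1.7% on the standard error and a one-sided error of about 5.3% under planned recruitment. The 4.4% and 5.8% need 5 controls per GP, which is the sample size section's cluster size but not what 40 practices would yield.

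These figures assume an ICC of 0.05, one GP cluster per practice, about 5 participants per practice, and GP effects that act on the control treatment separately from any effect on podiatry patients. If GP effects are shared by both arms, the loss is essentially nil. Podiatrist clustering is explicitly covered, so it would be wrong to infer that the analysis ignores clustering in general, or that 75 per arm is inadequate on this ground.

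**What to change.** State the primary model as partially nested:

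- a random podiatrist effect in the podiatry arm only;
- a random GP or practice effect in the control arm, or equivalently in purpose a practice-by-treatment effect;
- participant-level repeated measures.

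A practice effect common to both arms is not enough by itself, because the variation at issue is specific to the control arm. If the investigators judge that a standardised leaflet leaves no room for GP clustering, they should say so, drop the level deliberately, and reword the Sample size section so that its ICC and cluster size apply to podiatrists only.

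The cost is a few lines of text and model code. Participants are recruited through practices and podiatrists complete a standard form, so the identifiers should be available. The downside is slightly wider intervals and possible convergence work, since many practices will supply only a few controls.

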### Primary and secondary outcome measures

The primary outcome measures will be forefoot pain intensity scored by the participant on an 11-point pain numerical rating scale (PI-NRS, where 0 = no pain and 10 = worst possible pain), foot function using the 5 point Foot Function Index (FFI-5pt) and foot disability using the FPDI [17,24,25]. The FFI-5pts has been translated into Dutch and validated for similar participants as an interview schedule. The FPDI has been validated for participants with foot problems but was not yet available in Dutch. Within the scope of this trial the FPDI has been translated into Dutch and will be validated according to methods proposed by Beaton et al.[26]. Secondary outcomes include social participation (Keele Assessment of Participation[27]) and Quality of Life (SF-12). Both primary and secondary outcome measures will be collected at baseline and after 3, 6, 9, and 12 months. Data on personal education and work history, shoe history and co-morbidity[28] are collected at baseline as possible effect modifiers or confounders.

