### Treatment allocation and adherence

After providing informed consent, randomisation will be performed based on an allocation schedule that is generated before the start of the trial by a computerised random number generator using block randomisation with blocks of 8 or 4 with pre-stratification for gender and age (<75, ≥ 75). Since the age group ≥ 75 is expected to be smaller, a block of 4 has been chosen to increase the likelihood of equal distribution over the control and intervention groups. An independent research assistant will prepare coded sealed envelopes containing the treatment allocation. After baseline measurements the correct allocation envelope is opened by the participant. The foot examiner will be blinded for the random sequence and will not be informed of the block size ensuring concealed allocation of treatment. All GPs will be notified about the participants' allocated treatment, and will be asked to stimulate adherence to treatment whenever the participant contacts the GP during the intervention period. If symptoms do not improve despite adherence to treatment during the 3 months following randomisation, or with deterioration of the foot problem, the GP is free to provide another treatment or refer the participant for further treatment elsewhere.

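### Baseline adjustment is triggered by observed imbalance, with no variable or criterion named, so the primary model is left open and the precision in the baseline score is not secured

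*Protocol article*

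**What the plan says.** The Data analysis section describes a multilevel model for the three primary outcomes. On model structure it says: "Both clustering due to participants being treated by podiatrists and clustering due to repeated measurements within the same individuals will be taken into account". On the target of estimation: "The effect of interest is the treatment × time interaction", with the main focus on 3 and 12 months. On covariates its only statement is: "Results will be adjusted for differences in baseline similarity, if these occur". It does not say which variables are compared, how a difference is judged, or which model results.

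Under Treatment allocation and adherence, the allocation uses "block randomisation with blocks of 8 or 4 with pre-stratification for gender and age (<75, ≥ 75" years). The Data analysis section neither includes nor excludes these two factors.

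Under Primary and secondary outcome measures, the primary outcomes are measured at baseline and at 3, 6, 9 and 12 months. Data on education and work history, shoe history and co-morbidity "are collected at baseline as possible effect modifiers or confounders". The Trial design section describes the trial as open.

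**The concern.** The article states a rule, and the rule is the problem. A fuller analysis plan that followed it faithfully would still adjust only when the arms looked different.

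In a properly randomised trial, baseline differences between arms arise by chance. A covariate earns its place by predicting the outcome, and observed imbalance is a poor guide to that. Three consequences follow.

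- **Discretion.** With no variable list and no threshold, two analysts could reach different primary models from the same data, in a trial where allocation is known.
- **Precision.** The baseline value of each outcome is the one covariate for which the article gives a predictive strength (correlation 0.50). Under the rule it enters as a covariate only if the arms happen to differ on it.
- **Stratification factors.** Stratifying by gender and age group tends to balance them. A rule triggered by imbalance is therefore least likely to pick up the very factors the design treated as important.

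**Working it through.** **Inputs (Sample size section).** Difference 1 point at 12 months; SD 2.5; "with a one-sided significance level of 0.05"; power 0.8; ICC 0.05; 5 patients per care provider; correlation r = 0.50 between repeated measurements; 75 completers per arm. The Data analysis section gives a 5% level without repeating the sidedness, so I use the one-sided level throughout.

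**The plan's own figure.** The basic formula is n = 2 × (2.5 × (1.645 + 0.842))² / 1² = 77.3 per arm. The design effect is 1 + (5 − 1) × 0.05 = 1.2.

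- With the design effect and no use of r: 77.3 × 1.2 = 92.7, so 93 per arm.
- With baseline as a covariate (variance factor 1 − r² = 0.75): 92.7 × 0.75 = 69.6, so 70 per arm.

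No one-sided variant tried gave 75. The article gives no formula, so this is a side observation and carries no weight in the point. The last step, 75 / (1 − 0.25) = 100, is exact.

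**Variance factors at r = 0.50, assuming equal variances over time.**

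- Follow-up score, unadjusted: 1.
- Change from baseline: 2(1 − r) = 1, the same as unadjusted.
- Baseline as a covariate: 1 − r² = 0.75.
- Baseline as a time point with a separate mean in each arm: the treatment × time contrast is a change score, factor 1.
- Baseline as a time point with a common mean across arms: about 0.75.

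**Power at 75 per arm, 12-month contrast.** SE = 2.5 × √(2 × D × V / 75), where D is the design effect and V the variance factor. Power = Φ(1/SE − 1.645).

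| Design effect | V = 1: SE, power | V = 0.75: SE, power |
|---|---|---|
| 1.2 in both arms | 0.447, 72.3% | 0.387, 82.6% |
| 1.2 in one arm (average 1.1) | 0.428, 75.5% | 0.371, 85.4% |
| None | 0.408, 78.9% | 0.354, 88.2% |

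The covariate factor depends on r: it is 0.91 at r = 0.3 and 0.51 at r = 0.7.

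**Where the conditional rule falls.** The article gives no threshold, so I assume adjustment for the baseline score when its between-arm test gives p < 0.05. A simulation of 100,000 trials (75 per arm, r = 0.50, no clustering) gave:

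| Analysis | SE | Power | One-sided type I error |
|---|---|---|---|
| Never adjust | 0.408 | 78.4% | 5.0% |
| Adjust if p < 0.05 | 0.394 | 79.5% | 4.6% |
| Always adjust | 0.354 | 87.6% | 5.0% |

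The trigger fired in about 5% of trials, so under this threshold the rule behaves almost like no adjustment. All three estimates were unbiased. A looser threshold would move the rule towards the bottom row.

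**Stratification factors.** The article gives no figure for how well gender and age predict the outcomes, so their gain cannot be computed. As an illustration only, if they explained an assumed 0 to 5% of the remaining variance, the requirement would move from 69.6 to 69.6 × 0.95 = 66.1 per arm.

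**The case against.** The strongest defence is that the baseline outcome may already be in the model. Outcomes are measured at baseline and four later visits, and the target is a treatment × time interaction, so baseline is naturally read as one of the time points. The adjustment sentence would then concern other variables. This stands in part. If the model holds the baseline mean equal across arms, the precision is already recovered. If each arm has its own baseline mean, the contrast is a change score and at r = 0.50 gains nothing. The article does not say which.

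Several stronger readings are tempting and are not supported.

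- *The stratification factors are left out of the model.* No passage says so. This is a condensed article, and a covariate list may sit in a fuller document. What the text supports is that they are not named and that the stated rule tends to pass them by. A percentage for over-large standard errors has no source in the article.
- *The trial has only 72% power.* That is one scenario, comparing never with always adjusting at 12 months. The correlation of 0.50 is a listed sample-size input, so the planners used it somehow. If the target were the average over four follow-ups, with a constant effect and equal correlations, the factor would be (1 + 3 × 0.5)/4 = 0.625. Power would then be about 88% with design effect 1.2 and no baseline adjustment.
- *The rule inflates type I error or biases the estimate.* A fixed rule on one covariate did neither in the simulation. Free choice among several covariates is a fair worry, but it has not been quantified.
- *The education, shoe and co-morbidity items are the pool for the rule.* The article calls them possible effect modifiers or confounders; it does not link them to the adjustment sentence.

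**Conclusion.** The point holds as a badly fixed rule. Adjustment depends on observed differences, with no variable or criterion, so the primary model is open until baseline data are seen. Use of the baseline score to reduce variance is left to chance unless a common baseline mean is imposed.

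In the trial's own inputs, always including baseline is worth about 9 to 10 points of power for the 12-month contrast: 72% to 83%, 76% to 85%, or 79% to 88%, according to how the design effect is applied. These figures rest on r = 0.50, equal variances over time and a one-sided 0.05 test. They bound the loss; the conditional rule lies somewhere between the two ends. The gain from gender and age group is unknown and may be small. The change should be made, but the trial's validity does not hang on it.

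**What to change.** Replace the adjustment sentence in the Data analysis section with:

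> Every model includes the baseline value of that outcome (as a covariate, or through a common baseline mean across arms) and the stratification factors gender and age (<75, ≥75), whatever the observed balance. No covariate is chosen on observed imbalance; any other adjustment is a sensitivity analysis.

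The cost is one sentence, fixed before outcome data are seen. The baseline scores are already collected, and gender and age group are already recorded for the randomisation, so no participant, visit or measurement is added.

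### The Data analysis section names both an overall effect and a treatment × time interaction as its target, and only one form of that interaction is the 12-month contrast the trial is sized for

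*Protocol article*

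**What the plan says.** In the protocol article, the Data analysis section opens with an averaged target: "Multilevel analysis will be used to estimate the overall effect of podiatric treatment as compared to standardised shoe advice on the three primary outcome measures". Later in the same paragraph it names another: "The effect of interest is the treatment × time interaction". The rest of that sentence puts the emphasis on two visits, month 3 and month 12. On baseline it says: "Results will be adjusted for differences in baseline similarity, if these occur".

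The Sample size section works from a third expression: "In order to detect a 1 point difference in improvement between the groups after 12 months with a one-sided significance level of 0.05". The planned difference is 1 point (improvement of about 2 versus 1), with an SD of 2.5.

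The section on outcome measures gives the schedule: "Both primary and secondary outcome measures will be collected at baseline and after 3, 6, 9, and 12 months". The article does not say whether time enters as categories or as a line, or whether the baseline score is one of the modelled outcomes.

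**The concern.** An overall effect averages the group difference over visits. A treatment × time interaction describes how that difference changes over time. The two are different quantities, and one paragraph gives both as the target. Whether the interaction is also the 12-month difference used for the sample size depends on how the model is set up:

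- Baseline among the outcomes, time categorical: the 12-month interaction term is exactly the difference in improvement at 12 months.
- Baseline as a covariate, only follow-up visits as outcomes: a benefit of equal size at 3, 6, 9 and 12 months gives an interaction of zero.
- Baseline among the outcomes, time linear: a benefit that is complete by month 3 is fitted by a straight line and diluted.

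The conditional baseline adjustment adds to this. If it is carried out by moving the baseline score to the covariate side, the named effect could change its meaning according to a chance imbalance. At stake are what the primary test estimates and how much power it has.

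**Working it through.** **Inputs from the article (Sample size):** difference 1 point; SD 2.5 (variance 6.25); correlation r = 0.50; ICC 0.05; 5 patients per provider; one-sided 0.05; power 0.8; 75 per arm with complete data; 25% drop-out. Visits at 0, 3, 6, 9 and 12 months.

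**Assumptions added here:** compound symmetry; SD 2.5 at each visit (with r = 0.5 the change-score SD is then √(2 × 6.25 × 0.5) = 2.5 as well); design effect 1 + (5 − 1) × 0.05 = 1.2 in both arms, so 75/1.2 = 62.5 effective patients per arm; group differences of (0, 1, 1, 1, 1) over the five visits.

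**1. The article's own figure.** n = 2 × 6.25 × (1.645 + 0.842)² / 1² = 77.3, so 78 per arm without clustering.
- Change score with design effect: 77.3 × 1.2 = 92.7, so 93.
- Baseline-adjusted with design effect: 77.3 × 0.75 × 1.2 = 69.6, so 70.

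With the design effect, the stated 75 lies between these two and equals neither. The drop-out step reproduces: 75/0.75 = 100. The mismatch is a separate matter and does not decide this point.

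**2. Interaction across follow-up visits only.** Centred times are (−4.5, −1.5, 1.5, 4.5). Their product with (1, 1, 1, 1) sums to 0, so the expected interaction is 0 and power equals alpha, 5%.

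**3. Linear interaction, baseline included.** Centred times are (−6, −3, 0, 3, 6), with sum of squares 90. Slope = (−3 + 0 + 3 + 6)/90 = 6/90 = 0.0667 per month, or 0.80 points over 12 months. SE of the slope = √(2 × 6.25 × 0.5 / (90 × 62.5)) = 0.0333. Power = Φ(0.0667/0.0333 − 1.645) = Φ(0.355) = 64%.

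**4. Categorical time, baseline included, 12-month term.** Expected value 1.0. SE = √(2 × 6.25 / 62.5) = 0.447. Power = Φ(2.236 − 1.645) = 72%.

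**5. 12-month difference with baseline as covariate.** Variance 6.25 × (1 − 0.5²) = 4.69. SE = √(2 × 4.69 / 62.5) = 0.387. Power = Φ(2.582 − 1.645) = 83%.

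**6. Average of the four follow-ups with baseline as covariate** (one natural form of an overall effect). Variance 6.25 × [(1 + 3 × 0.5)/4 − 0.25] = 2.34. SE = √(2 × 2.34 / 62.5) = 0.274. Power = Φ(3.651 − 1.645) = 98%.

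| Target | Expected value | Power, design effect 1.2 | Power, no design effect |
|---|---|---|---|
| Interaction, follow-ups only | 0 | 5% | 5% |
| Linear interaction with baseline | 0.8 | 64% | 71% |
| Categorical 12-month term with baseline | 1.0 | 72% | 79% |
| 12-month difference, baseline covariate | 1.0 | 83% | 88% |
| Average follow-up difference, baseline covariate | 1.0 | 98% | 99% |

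**7. Other shapes over time** (design effect 1.2). If the benefit grows in a straight line to 1 point at 12 months, the linear interaction has 80% power, against 72% for the categorical term and 83% for the baseline-adjusted contrast. If it starts at 1 point and fades (0, 1, 0.83, 0.67, 0.5), the linear interaction implies (−3 + 3 × 0.67 + 6 × 0.5)/90 × 12 = 0.27 points at 12 months, against a true 0.5.

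**The case against.** The best defence is that the interaction sentence does not stop at the interaction. It goes on to place the focus on two named visits, which points to visit-specific terms rather than a single slope or a test of equality across visits. Baseline is collected as part of the same series, and an adjustment made only when imbalance appears fits poorly with a standing baseline covariate. Read that way, the 12-month term is the difference in improvement that the trial is sized on, and a benefit present from month 3 appears in full. This stands. A reader might infer that the interaction can never be the 12-month difference, or that the plan is bound to miss a constant benefit. The article does not support either inference.

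Other parts of the defence also stand. The 5% and 64% figures each need a model form that the article does not state. A benefit constant from month 3 is an assumption: the article mentions a progress check at six to eight weeks but says nothing about the shape of the effect, and it allows a change of treatment after 3 months without improvement. The gap from 72% to 83% comes from how baseline is used, not from choosing an interaction as such. A provider effect that is constant over time would cancel from change and slope contrasts, so the design effect may be too harsh there; without it the categorical term has 79%. Finally, time coding alone is detail that a journal article may leave to a fuller plan.

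What the defence does not remove is the conflict in the text itself. The paragraph names two targets that are not synonyms, and it makes baseline adjustment depend on observed imbalance. Those are statements, not omissions.

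**Conclusion.** The point holds as a conflict of targets, of moderate severity. The overall effect, the treatment × time interaction and the 12-month difference in improvement are not one quantity. The last two coincide only with baseline among the repeated outcomes and categorical time. For the same constant 1-point benefit, forms that the paragraph admits range from 5% to 98% power. The benign form, at about 72%, is still less precise than a baseline-adjusted 12-month contrast at about 83% (79% and 88% without the design effect).

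These figures concern the pain scale only and rest on 75 per arm, SD 2.5, r = 0.5, compound symmetry and an assumed time course. They show the cost of leaving the form open. They do not show that the trial has adopted the form with no power, and it would be wrong to say that the plan cannot estimate what it is sized for.

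**What to change.** Replace the two statements of the target with one:

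- **Primary contrast:** the between-group difference at 12 months, as used in the Sample size section, for each primary outcome.
- **Model:** multilevel, on the 3, 6, 9 and 12-month scores, with time as categories, treatment and treatment × visit terms, and the clustering already planned.
- **Baseline:** the baseline score is always a covariate, whether or not the groups differ on it.
- **Secondary:** the 3-month difference and the average difference over follow-up.
- **Descriptive only:** the joint test of the treatment × visit terms.

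The 12-month visit is proposed because the article sizes the trial on it. The average difference has more power under a constant benefit but answers another question. The cost is a few sentences, written before outcome data are examined, with no extra patients, visits or software. If the visit-specific reading was intended all along, the change writes it down and gains precision through the fixed baseline covariate.
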